### Description of Intervention Conditions

#### LIFE-DM Intervention

LIFE-DM is a 12-session group therapy. BA and PST focused on mood management and livelihood problems. The first 8 sessions are delivered once a week, and the remaining 4 sessions are delivered every other week, with the program usually lasting 4 to 5 months. BA is an evidence-based treatment that focuses on increasing pleasurable and meaningful behavior in order to improve mood. The theory underlying BA is that depression is maintained by environmental and behavioral factors (eg, a lack of appropriate social skills) that decrease pleasant or rewarding activities. Therefore, BA aims to improve mood by increasing engagement in positive activities and reducing activities that sustain depressed mood or hinder adaptive activities. This is achieved through techniques, such as mood monitoring, activity scheduling, and engagement in pleasurable and healthy activities [33]. PST, a cognitive-behavioral approach, provides a structured and positive method for tackling real-life challenges [34]. PST empowers individuals to better understand and manage their problems by teaching them how to accurately define and prioritize problems, brainstorm effective solutions, and take actionable steps to solve them.

In LIFE-DM, BA and PST are integrated with livelihood training. All microfinance services were provided by the Vietnamese Women’s Union (WU), which has been the primary distributor of microfinance initiatives in Vietnam since 1987, serving as the interface between banks and impoverished women. The WU has significant expertise in implementing microfinance programs and has been supported internationally by the World Bank, AusAID, the International Women’s Development Agency, and the Vietnamese government. In Da Nang, WU has operated a microfinance program since 1987 with over 60 trained staff.

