### Power Analysis

The primary outcomes are treatment engagement, depression symptom change in PHQ-9 score, and depression remission on the Mini International Neuropsychiatric Interview (MINI). We compare the means in a regression framework, after taking into account the design effect induced by clustering, to determine the power when comparing the intervention group to the control group. We note that the end-status analysis assumed for the power calculations can be conservative because it does not use all 3 waves of data and uses only the projected retained sample at month 12. For the power analyses, we used the conservative estimate of the projected retention rate of 79% at the 12-month follow-up. This translates to approximately 64 patients per condition at the 12-month follow-up. A recent meta-analysis found an effect size of 0.78 favoring therapies using BA over control conditions using professionals [40]. However, given the use of paraprofessionals with limited mental health training, we expect smaller effect sizes. For these power analyses, we used conservative effect sizes of 0.3 and 0.4. Since patients are clustered within intervention groups, patients’ outcomes may be correlated, even though other randomized mental health studies have found intraclass correlation coefficients that are essentially zero [41]. Using this effect size, a power of 0.85, a conservative intracluster correlation of 0.1, a cluster size of 10, and a design effect of at least 2, we determined that 142 participants were needed for the study. Calculations were performed using sampsi and sampclus commands on STATA [42]. To account for loss to follow-up, we planned to enroll 160 and ended up with a final sample size of 166 participants.

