### Outcome Measures

All study measures (Table 1) were adapted using a consensus approach to ensure linguistic and cultural appropriateness for use in Vietnam. Primary outcomes focused on depression severity and diagnosis, measured by the PHQ-9 [38], which assesses depressive symptom severity, and severe mental illness screener, which was based on items from the MINI [43]. Secondary outcomes included program participation indicators, such as group attendance, engagement in livelihood activities, and acceptance of depression care. The data were gathered through face-to-face surveys, clinic logs, and program records.

**Table 1. T1:** Main outcome measures.

Indicator	Scale or measure	Data source
Depression severity	Patient Health Questionnaire	Surveys at baseline, 6 months, and 12 months
Anxiety severity	Generalized Anxiety Disorder	Surveys at baseline, 6 months, and 12 months
Health functioning	Short-form Health Survey	Surveys at baseline, 6 months, and 12 months
Quality of life	Quality of Life Enjoyment and Satisfaction Questionnaire	Surveys at baseline, 6 months, and 12 months
Behavioral activation	Brief Activation for Depression Scale–Short Form	Surveys at baseline, 6 months, and 12 months
Social capital	Short Social Capital Assessment Tool	Surveys at baseline, 6 months, and 12 months
Program participation	Group attendance, engagement in livelihood activities, and acceptance of depression care	Clinic logs or program records

Anxiety symptoms were assessed using the 7-item Generalized Anxiety Disorder 7 scale (GAD-7) [44]. Health functioning was measured by the Short Form-12 Health Survey [45], capturing both physical and mental health status. Quality of life was assessed with the Quality of Life Enjoyment and Satisfaction Questionnaire [46], while BA was evaluated using the Brief Activation for Depression Scale–Short Form [47], which captures levels of engagement in goal-directed activities. Social capital was measured using an adapted version of the Short Social Capital Assessment Tool [48], which includes indicators of community participation and support. Economic and employment outcomes included measures of work status, income, household assets, loan and savings activities, and perceived performance of small businesses. Additional sociodemographic covariates such as age, marital status, education, mental health literacy, household size, and number of dependents were also collected to adjust for potential confounders.

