We will examine variable distributions from all time points to assess missing data patterns within each study wave and replace them with information gathered from clinic logs and program records. Based on previous similar studies in Vietnam in general and Da Nang in particular, we expect response rates of approximately 80% at 6-month and 12-month follow-ups, resulting in about 128 patients at the 2 follow-ups. All planned analyses will use likelihood methods, which are effective under missing at random assumptions [54]. This approach helps account for participants dropping out of the study while making the most efficient use of all the data collected. Because time will be a random effect within the mixed model analyses, participants without complete data will be included fully in the analyses. For all outcomes, Cohen *d* will be calculated to estimate the effect size using pooled SD of baseline scores. Two-sided *P*<.05 will be considered statistically significant.

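### The rule that replaces missing data from clinic logs and program records is not limited to variables those sources measure, and does not fit the likelihood analysis planned beside it

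*Protocol article*

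**What the plan says.** The Data Analysis section says that missing-data patterns will be examined within each wave and that the team will "replace them with information gathered from clinic logs and program records". It names no variable, arm, time window or mapping from record to survey item.

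The same paragraph then states: "All planned analyses will use likelihood methods, which are effective under missing at random assumptions". It adds that, through the mixed model, "participants without complete data will be included fully in the analyses".

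Table 1 (Outcome Measures) assigns a source to each measure. The primary severity measure reads "Depression severity Patient Health Questionnaire Surveys at baseline, 6 months, and 12 months". Anxiety, functioning, quality of life, behavioral activation and social capital have the same source. Logs or records appear in one row only, program participation, described as "group attendance, engagement in livelihood activities, and acceptance of depression care". The MINI and the economic measures are not in Table 1. The text of that section names surveys, logs and records together as the trial's sources, without saying which of them supplies these two.

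On the amount of missing data, the article says "we expect response rates of approximately 80% at 6-month and 12-month follow-ups, resulting in about 128 patients".

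**The concern.** The waves are the three survey rounds: the Power Analysis section speaks of three waves, and Table 1 lists surveys at three time points. Participation, the one measure that Table 1 draws from logs and records, has no survey wave. A rule for filling gaps within waves therefore reaches the survey outcomes on its plain wording, including the primary PHQ-9, although Table 1 does not show the replacement source as holding them.

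Three things are at stake if the rule is applied that way. Values that differ in instrument or timing would enter the same outcome variable. They would be treated as observed, so the uncertainty they carry would not reach the standard errors. And the error could differ by arm, because some of the records exist only under LIFE-DM. Propensity weights built on baseline covariates cannot correct a measurement difference that arises after baseline.

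**Working it through.** **Share of data open to replacement.** The article plans on an 80% response and about 128 women, and it also says "we planned to enroll 160 and ended up with a final sample size of 166 participants".
- Planned enrolment: 160 × 0.80 = 128. The stated figure reproduces.
- Actual enrolment: 166 × 0.80 = 132.8, so the 128 rests on the planned 160.
- Expected missing per follow-up wave on the enrolled sample: 166 × 0.20 = 33.2, about 33 women. If missingness is equal by arm, this is 92 × 0.20 = 18.4 in LIFE-DM and 74 × 0.20 = 14.8 in E-TAU.

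**Which records exist in which arm.**
- LIFE-DM: 12 group sessions, "with the program usually lasting 4 to 5 months"; all sessions videotaped and rated (Adherence and Quality Assessment); optional study loans on a 20-month repayment schedule, with monthly meetings encouraged after the last session (LIFE-DM Intervention).
- E-TAU: medication offered, with possible referral to the Women's Union or other bodies (Enhanced Treatment as Usual).
- Both arms: medication assessment and management at the health station (same section).

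Group-session and study-loan records thus arise in LIFE-DM only, while clinic contact for medication exists in both. Nothing states how complete any of these records are.

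**Illustrative shift in the arm difference.** Let m be the missing share, f_L and f_E the shares of missing values filled in LIFE-DM and E-TAU, and e the mean error of a filled value in PHQ-9 points, taken as equal in both arms. Then

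shift = m × (f_L − f_E) × e, and d = shift / SD.

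From the article: m = 0.20 and SD = 3.46 (baseline PHQ-9, Table 2). Assumed, because the article gives no value: e of 1, 2 or 3 points, and the three filling patterns.

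| Filled, LIFE-DM vs E-TAU | e = 1 | e = 2 | e = 3 |
|---|---|---|---|
| Equal (50% vs 50%) | 0 | 0 | 0 |
| 80% vs 20% | 0.20 × 0.60 × 1 = 0.12 (d 0.03) | 0.24 (d 0.07) | 0.36 (d 0.10) |
| 100% vs 0% | 0.20 × 1 × 1 = 0.20 (d 0.06) | 0.40 (d 0.12) | 0.60 (d 0.17) |

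The sign follows the sign of e, which is unknown. For scale, the planning effects of d 0.3 and 0.4 equal 0.3 × 3.46 = 1.04 and 0.4 × 3.46 = 1.38 points. With no replacement of survey outcomes, the shift from this source is zero by construction.

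**The case against.** The strongest reply is that the sentence is only loosely worded. If logs and records hold participation data alone, they contain no PHQ-9 or MINI value to insert, and the rule can do no harm to the primary outcome. It may mean no more than retrieving facts the records do hold, such as attendance or a loan taken, with the likelihood model handling the rest. Retrieving a recorded fact recovers data; it is not imputation. The variable-by-variable mapping could also sit in a fuller document.

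Much of this stands. The article does not show that logs held PHQ-9 or MINI values in the main trial. PHQ-9 collection alongside group attendance is described for the pilot only, and pilot participants were excluded. Women's Union records may be a good source for loan and savings items, given that the article itself acknowledges bias in self-reported income. What does not stand is that the matter is merely missing detail: the article gives a positive instruction, scoped to the survey waves, that conflicts with its own source table and is not reconciled with the likelihood approach that follows.

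A reader might go further and infer that LIFE-DM records are far fuller, that filled values would look better there, and that the primary comparison is biased toward the intervention by a large part of the planned effect. The article does not support this. It does not report record completeness by arm or say who keeps the records. Clinic contact occurs in both arms, and loan records can extend past months 6 and 12. Women who miss a survey may be those who stopped attending and so have sparse session records. A value from mid-programme could be worse or better than the later one.

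**Conclusion.** The point holds as a conditional one. As written, the rule is unrestricted, is at odds with Table 1, and is unnecessary for survey outcomes under the likelihood analysis planned in the same paragraph. Applied to those outcomes, it would introduce non-equivalent values treated as observed, with an error that could differ by arm.

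The size and direction cannot be determined. The illustrative range runs from no shift to d 0.17. It rests on equal missingness of 20%, an equal assumed error of 1 to 3 points in both arms, and assumed filling patterns; the upper end needs every gap filled in LIFE-DM and none in E-TAU. It should be read as showing why the rule needs a limit, not as a forecast of bias in favour of LIFE-DM.

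**What to change.** Restate the rule in four parts:

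1. Replace missing values from logs and records only for variables those sources directly record: program participation, and loan or savings items where the record matches the survey item and time point in both arms.
2. Leave missing PHQ-9, MINI, GAD-7 and other survey scales to the likelihood model fitted to observed survey data.
3. For those outcomes, use logs and records only as auxiliary variables or in a sensitivity analysis labelled as such.
4. Report missingness by arm at each wave.

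The cost is a change of wording and slightly fewer non-missing values in the main analysis. No new data are needed, and the article describes the analysis as still in progress.

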### Ethical Considerations

This study was approved by the Da Nang Psychiatry Hospital Institutional Review Board (01/17/HDDD) and the RAND Corporation (2012‐0031 RAND IRB). The study was conducted in accordance with the Declaration of Helsinki. All participants provided written informed consent before participating in the study. Participants received 50,000 VNĐ (approximately US $2.30) for completing each survey as compensation for their time. All participant data will be deidentified and assigned unique study identification numbers prior to analysis.

## Results

### Participant Flow

This study was funded prior to implementation, and the data were collected from February 2014 to September 2015. A total of 198 women were screened for eligibility, of whom 166 met the inclusion criteria and were enrolled. Thirty-two women were excluded for the following reasons: outside the eligible age range (n=3), income above the threshold (n=4), PHQ-9 score below 10 (n=8), elevated suicide risk (n=1), declined participation prior to consent (n=14), or withdrew after consenting (n=2; Figure 1). Baseline characteristics of participants are presented in Table 2. Data analysis is in progress, and the findings are expected to be disseminated in 2027.

**Figure 1. F1:**
[figure not shown]
LIFE-DM trial flow chart. E-TAU: enhanced treatment as usual; LIFE-DM: Livelihood Integration for Effective Depression Management; PHQ-9: 9-item Patient Health Questionnaire.

**Table 2. T2:** Participants’ baseline characteristics and group differences^a^.

Indicators	Overall (N=166)	E-TAU^b^ (n=74)	LIFE-DM^c^ (n=92)	*P* value
Demographics				
Age, mean (SD)	42.27 (8.37)	42.72 (8.59)	41.91 (8.23)	.54
Marital status (currently married), n (%)	119 (71.69)	53 (71.62)	66 (71.74)	.99
Size of household, mean (SD)	4.43 (1.53)	4.43 (1.46)	4.42 (1.59)	.97
Number of children, mean (SD)	2.29 (1.04)	2.24 (1.06)	2.33 (1.04)	.61
Number of children ages 5‐18 (y), mean (SD)	1.14 (0.91)	1.18 (0.87)	1.11 (0.94)	.64
Reading ability (can read easily), n (%)	135 (81.33)	56 (75.68)	79 (85.87)	.094
Writing ability (can write easily), n (%)	131 (78.92)	53 (71.62)	78 (84.78)	.04
Education level (completed primary school), n (%)	122 (73.49)	47 (63.51)	75 (81.52)	.009
Economic factors				
Home ownership, n (%)				.46
Does not own home	60 (36.14)	29 (39.19)	31 (33.70)	
Owns home	106 (63.86)	45 (60.81)	61 (66.30)	
Monthly income (US $), mean (SD)				
Family income	169.94 (82.10)	166.36 (87.74)	172.82 (77.65)	.62
Individual income	82.35 (53.83)	71.1 (54.40)	91.83 (51.78)	.02
Household per capita income	40.52 (18.93)	39.42 (20.02)	41.41 (18.07)	.50
Poverty (World Bank threshold), n (%)	49 (29.52)	27 (36.49)	22 (23.91)	.08
Employed, n (%)	120 (81.63)	39 (68.42)	81 (90.00)	<.001
Owned business in past, n (%)	68 (40.96)	18 (24.32)	50 (54.35)	<.001
Currently owns business, n (%)	59 (35.54)	16 (21.62)	43 (46.74)	<.001
Currently has loans, n (%)	79 (47.59)	37 (50.00)	42 (45.65)	.58
Current loan amount (US $), mean (SD)	700.12 (1083.26)	482.95 (693.33)	890.80 (1315.01)	.10
Currently saves money, n (%)	31 (18.67)	12 (16.22)	19 (20.65)	.47
Current amount saved (US $), mean (SD)	189.85 (410.87)	337.88 (628.18)	91.16 (82.86)	.11
Mental health				
PHQ-9^d^ score (0‐27), mean (SD)	14.43 (3.46)	14.28 (2.95)	14.54 (3.83)	.63
Currently have depression (MINI^e^), n (%)	141 (85.45)	57 (78.08)	84 (91.30)	.02
Had depression in the past (MINI), n (%)	110 (66.67)	45 (61.64)	65 (70.65)	.22
GAD-7^f^ (0‐21), mean (SD)	9.58 (3.52)	9.03 (2.79)	10.01 (3.96)	.08
Psychosocial				
BADS-SF^g^ (0‐54), mean (SD)	21.02 (3.99)	20.81 (4.08)	21.20 (3.92)	.54
Experienced domestic violence, n (%)	44 (26.51)	21 (28.38)	23 (25.00)	.62
Q-LES-Q^h^ (0‐100), mean (SD)	28.83 (9.18)	27.99 (8.69)	29.50 (9.55)	.30
MOS-SF-12^i^ physical component, mean (SD)	36.77 (5.28)	36.94 (4.87)	36.63 (5.61)	.71
MOS-SF-12 mental component, mean (SD)	27.33 (7.05)	27.42 (6.10)	27.25 (7.77)	.88
MOS-SF-12 total (0‐100), mean (SD)	35.06 (22.10)	32.6 (23.95)	37.05 (20.40)	.20
Structural social capital support (including both active group and social support), n (%)				.04
None	54 (33.96)	32 (44.44)	22 (25.29)	
One	36 (22.64)	15 (20.83)	21 (24.14)	
Two or more	69 (43.40)	25 (34.72)	44 (50.57)	
Structural social capital (active group membership only), n (%)				.06
None	92 (55.42)	48 (64.86)	44 (47.83)	
One	61 (36.75)	23 (31.08)	38 (41.30)	
Two or more	13 (7.83)	3 (4.05)	10 (10.87)	
Business self-efficacy (0‐10), mean (SD)	6.26 (1.51)	5.89 (1.45)	6.56 (1.50)	.005
Goal self-efficacy (4-20), mean (SD)	9.74 (2.28)	9.23 (2.07)	10.15 (2.38)	.01
Structural barriers to care, mean (SD)	4.27 (2.19)	4.78 (1.88)	3.87 (2.35)	.008
Mental health literacy, n (%)	72 (43.37)	28 (37.84)	44 (47.83)	.20
Depression stigma, mean (SD)	26.17 (3.00)	25.81 (3.60)	26.47 (2.39)	.17
Patient satisfaction, n (%)				
With CHS^j^	17.98 (1.13)	17.98 (0.97)	17.98 (1.25)	.99
With Women’s Union	18.13 (1.33)	17.69 (0.48)	18.29 (1.51)	.17

a The data in this table are not adjusted for survey design. Numbers do not all sum to 166 because of item nonresponse or not applicable. The percentages are not all 100% due to rounding.

b E-TAU: enhanced treatment as usual.

c LIFE-DM: Livelihood Integration for Effective Depression Management.

d PHQ-9: 9-item Patient Health Questionnaire.

e MINI: Mini International Neuropsychiatric Interview.

f GAD-7: 7-item Generalized Anxiety Disorder.

g BADS-SF: Behavior Activation for Depression Scale Short Form.

h Q-LES-Q: Quality of Life Enjoyment and Satisfaction Questionnaire.

i MOS-SF-12: 12-item Medical Outcomes Study Short Form.

j CHS: community health station.

### Baseline Characteristics

Among the 166 participants enrolled in the study (Table 2), the average age was 42 (SD 8) years. Most women were married (n=119, 71.69%). The majority of participants were able to easily read (n=135, 81.33%) and write (n=131, 78.92%), and 73.49% (n=122) completed primary school. Most women were employed (n=120, 81.63%). On average, the per capita family income was US $40.52 (SD 18.93) per month, and individual income was US $82.35 (SD 53.83) per month. In addition, 29.52% (n=49) lived below the poverty level according to World Bank 2010 criteria for Vietnam (653,000 VNĐ per person per month, or US $1 per person per day). Approximately 47.59% (n=79) reported having existing loans.

The mean score on the PHQ-9 scale for depression was 14.43 (SD 3.46), and 9.58 (SD 3.52) on the GAD-7 scale for anxiety. Most participants had a current diagnosis of depression (n=141, 85.45%). In terms of social capital support, 55.42% (n=92) of the participants had no active memberships in any social groups in the community, and 33.96% (n=54) of the participants reported having no source of social support (including both organizations and individuals). Participants reported an average of 4.27 (SD 2.19) structural barriers to care, such as transportation, money, and child-care responsibilities. In addition, participants reported a mean depression stigma score of 26.17 (SD 3; possible range is 0-40), where higher scores indicate higher perceptions of stigma.

In terms of economic characteristics, the groups differed with regard to business ownership and employment status, with women in the intervention group more likely to have prior experience owning a business (n=50, 54.35% vs n=18, 24.32%; *P*<.001), currently owning a business (n=43, 46.74% vs n=16, 21.62%; *P*<.001), and currently working (n=81, 90% vs n=39, 68.42%; *P*<.001). Those in the intervention group had higher individual income (US $91 per month vs US $71 in the control group; *P*=.02), but there were no significant differences between the groups by family income.

In terms of mental health characteristics, the intervention group was found to have a higher percentage who met the criteria for depression (n=84, 91.30% vs n=57, 78.08%; *P*=.02) according to the MINI Diagnostic Interview. However, severity scores on the PHQ-9 did not differ between the 2 groups. Participants in the intervention group also reported a lower mean number of structural barriers to care (3.87 vs 4.78; *P*=.008) and higher goal self-efficacy (10.15 vs 9.23; *P*=.01), as well as business self-efficacy (6.66 vs 5.74; *P*=.005).

## Discussion

### Study Rationale and Implications

The LIFE-DM trial aims to evaluate whether an integrated depression care and livelihood intervention can increase treatment engagement and is more effective than E-TAU in a collaborative care approach. The study addresses a critical gap in global mental health: how to effectively deliver evidence-based depression care to populations burdened by both mental illness and poverty. Despite the strong relationship between depression and poverty [3], this combined approach to care has not been previously evaluated in a controlled study. Many individuals in resource-poor settings face barriers to mental health care [15,16], including lack of awareness and knowledge about depression and depression care, stigma about mental health treatments, cost, economic stressors, and lack of value placed on mental health treatment. The LIFE-DM model is designed to integrate psychosocial support with financial empowerment, through microfinance activities, vocational training, and savings programs, to increase the acceptability and perceived value of depression treatment. This integrated approach is hypothesized to improve mental health, functional status, and economic well-being. If effective, this model may offer a scalable approach for similar low-resource settings.

This model is informed by principles of “stepped care” and “community-partnered process,” which emphasize accessible, acceptable, and contextually grounded interventions [55]. By incorporating income-generating activities, vocational support, and microfinance opportunities, the intervention may help reframe depression care as a means of improving broader life circumstances, thus reducing stigma and enhancing uptake [22]. It is anticipated that this integrated approach will increase the perceived relevance and acceptability of mental health interventions, especially among populations that view mental illness through social and economic lenses rather than clinical ones.

Furthermore, our findings are expected to contribute to the growing field of task-shifting in global mental health [17]. By engaging paraprofessional providers, WU, and CHS staff, the intervention explores the potential for extending the collaborative care models to settings with limited specialist resources. This approach aligns with broader efforts to strengthen health systems through decentralization, community-based services, and the use of nonspecialist providers. The findings from this study may help inform the development of scalable models for delivering evidence-based depression care in resource-limited contexts.

